## Discussion

This present protocol paper describes the design of a multidisciplinary, multicenter study, focused on Swedish short-term care, and we include a second, randomized case-controlled interventional study. This project has two important aims. First, it aims to describe important aspects of oral health, swallowing ability, and eating ability in older individuals, and to investigate the feasibility and effects of a program of oral screen training for dysphagia. Second, the project aims to study the quality of oral health-related care, as perceived by older individuals and staff in the short-term care units. The results of this project will provide important new knowledge for the development of short-term care for older individuals, in this specific care context, which has not been explored before. These resulting descriptions of the strengths and weakness in the quality of oral care will provide a basis for establishing guidelines for improving oral care in short-term care units. Moreover, in this context, the results of the swallowing training program with an oral screen will indicate whether this program will promote improvements in short-term care for this older population.

### Methodological considerations

Methodological and ethical problems were previously reported as challenges that explained the lack of empirical studies conducted in the short-term care context [16]. Therefore, the present project includes several strategies to increase the probability of succeeding and to strengthen the results, as follows: (1) only participants with sufficient cognitive capacity are included; (2) older individuals in end-of-life care are excluded; (3) multiple short-term care units are included, housed in various settings and located in different parts of Sweden; (4) a cluster randomization trail design is implemented; (5) both clinical and self-reported assessments are considered; (6) the data collectors are professionals that hold relevant clinical experience in communicating with older individuals and assessing their oral health and swallowing ability; in addition the research team has experience in the care context, where the data will be collected.

By minimizing methodological and ethical challenges, our results, regarding oral health status, swallowing, eating ability, and nutritional risk, might not be representative of all older people in short-term care, e.g., individuals in the highest risk categories will not be included. Other methodological challenges might arise when performing the intervention study with late follow-up assessments (six months). These challenges include accessing information on where the participant is located at the time of the follow-up; managing the high risk of drop-out, due to mortality, in the study population; and recruiting for part 2 of the study. The latter problem is expected, because older people might have low motivation to participate in swallowing rehabilitation, due to fatigue, or because they have adapted to their situation and find no use in training [6].

### Measurement tools

The minimal eating observation and nutrition form - version II (MEONF-II) [23, 24] is an easy-to-use, rapid, sensitive, screening tool that allows substituting of body mass index (BMI) with calf circumference, which increases its usability in this context, for assessing the risk of undernutrition. However, completing the form might be time-consuming for the nursing staff, and it requires a certain degree of familiarity with the older person.

The revised oral assessment guide (ROAG) [25, 26] is a systematic assessment tool for detecting problems related to teeth and dentures in older individuals. It was designed to be used by nursing staff, and it is well-documented in Sweden, because it is included in Senior Alert, the national registry of quality in geriatric care [27]. However, the assessment is performed solely with a mouth mirror and flashlight, not in a dental clinic.

The SCT [18] is a simple, easy-to use screening test for determining the risk of dysphagia in a non-hospital context. The SCT is a feasible tool for evaluating training paradigms for treating dysphagia [8]. The SCT requires an evaluation of age as a covariate, when performing data analysis.

Several self-assessment questionnaires (Table 1) will be used in the present study to evaluate QoL related to different health areas, including: the OHIP-14 [28, 29], the QPP-patient [19, 20], and the SWAL-QOL [30, 31]. These questionnaires will contribute multifaceted information from the perspectives of older individuals. The results will guide further improvements in QoL in the short-term care context. However, answering questionnaires might be exhausting for older people. Therefore, there might be a risk of bias, if older individuals require support in reading and interpreting the questions. However, this type of support might lead to more accurate responses and fewer drop-outs.

The QPP-staff is a modified version of the QPP-patient questionnaire [19, 20]. The QPP-staff will provide important knowledge, from the perspective of nursing staff members, about the quality of care for older individuals in short-term care units. The challenges for this instrument are the risks of hasty, incomplete responses and drop-outs among the nursing staff members expected to complete the questionnaires. Due to the working situations of nursing staff, the many other tasks and priorities related to patient care might compromise their compliance with study requirements.

The Katz-ADL instrument [32, 33] has been used in geriatric care since the 1960s. It is a simple tool for assessing functional status in older individuals. It enables evaluations of rehabilitation during follow-up and the prognosis of recovery after an illness. This tool is sensitive to broad changes in declining health status; however, it can be limited in its ability to measure small improvements in rehabilitation.

If our findings show that the swallowing intervention could be useful in this context (older individuals with various diagnoses complicated with dysphagia), the training method should be implemented as a treatment option for all older individuals with dysphagia. The staff in all types of geriatric care should be educated in implementing this method. Additionally, a successful swallowing intervention would provide benefits beyond the eating and swallowing abilities of the individual, because it would also reduce morbidity and mortality. We expect that a better understanding of oral health in the older population studied will highlight the unaddressed needs related to oral care and malnutrition. Moreover, our findings will provide important quality indicators of good oral health and eating-related nursing care, in short-term care units.

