### Sample size calculation

In study 2, the primary outcome variables will be the changes in swallowing capacity (based on the SCT), measured at the start and end of treatment, and at follow-up, 6 months later. The sample size calculation will be based on the assumption that the data will be normally distributed. To retain an overall type I error of 5%, the type I error will be set to 2.5% for the primary endpoint. Based on historical data, we assume that the standard deviation of the change in SCT level will be 3 ml/s. To detect a critical difference of 2.8 ml/s in swallowing capacity between the intervention and control groups with a power of 80% and type I error of 2.5%, a sample size of at least 22 subjects would be required to fulfill the study protocol in each group. The total number of subjects included must be somewhat higher, to compensate for drop-outs.

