### Statistical methods

The statistical package, IBM/SPSS®, will be used to perform all data analyses. *P*-values less than 0.05 will be considered statistically significant. Descriptive statistics will be used to describe eating ability, oral health status, swallowing ability, quality of oral care, and swallowing-related QoL, among older individuals admitted to short-term care units. Descriptive statistics will also be used to describe the staffs’ perceptions of care quality. Univariate, bivariate, and multivariable regression (linear and logistic) analyses will be used to evaluate the associations between various dependent and independent variables. The Bonferroni correction will be used when multiple, pair-wise tests are performed on a single set of data, to reduce the chances of obtaining type I errors. Continuous variables will be presented as the mean value and standard deviation; categorical variables will be reported as the median and interquartile range. Differences between groups (e.g., intervention vs. control, older individuals vs. staff) will be assessed with independent sample t-tests (for continuous variables), chi-square tests (for categorical variables), and ANOVA or Kruskal-Wallis (for more than 2 groups).

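### The protocol says SCT analysis requires age as a covariate, but the only test it names for intervention versus control on a continuous outcome is an unadjusted t-test

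*Protocol article*

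**What the plan says.** Sample size calculation in the protocol article defines the part 2 endpoint: "the primary outcome variables will be the changes in swallowing capacity (based on the SCT), measured at the start and end of treatment", and again at 6 months. The trial is sized on a two-group comparison of mean change, with a "critical difference of 2.8 ml/s in swallowing capacity between the intervention and control groups", and "we assume that the standard deviation of the change in SCT level will be 3 ml/s".

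Statistical methods covers both parts of the project in general terms. Differences between groups, with intervention versus control given as one example, "will be assessed with independent sample t-tests (for continuous variables"). No covariate is attached to that comparison. The same section lists linear and logistic multivariable regression, but for studying associations; it mentions neither the treatment contrast, nor age, nor baseline SCT.

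Measurement tools, in the Discussion, then sets a condition on any SCT analysis: "The SCT requires an evaluation of age as a covariate, when performing data analysis".

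Every part 2 participant has a baseline SCT value. An SCT below 10 ml/s is an entry criterion (Participants), and a failed teaspoon test is scored 0 ml/s (Table 1). Age is known because entry requires 65 years or more.

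**The concern.** The t-test named for the treatment comparison cannot meet the condition that the article itself sets for its primary outcome. An analyst who follows Statistical methods leaves age out; one who follows Measurement tools must use a different method. Two primary analyses are therefore open, with no rule for choosing between them before results are seen.

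A second matter follows from the same choice. The t-test on change subtracts baseline SCT with a coefficient of exactly 1. Part 2 selects people for low SCT, allocates them by care unit and plans about 22 per arm, so the arms may differ at baseline by chance. Where the true slope of follow-up on baseline is below 1, part of that difference passes into the estimated effect, and the standard error may be larger than it need be.

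**Working it through.** **1. The plan's own figure.** Inputs from Sample size calculation: difference 2.8 ml/s, SD of change 3 ml/s, power 80%, type I error 2.5%. Sidedness is not stated; two-sided reproduces the figure.

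n per arm = 2 × (z₀.₉₈₇₅ + z₀.₈₀)² × (3/2.8)² = 2 × (2.241 + 0.842)² × 1.148 = 21.8, so 22.

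This is the stated 22, and the formula is that of an unadjusted comparison of change. With the exact t distribution, power at 22 per arm is 77.7%.

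**2. The sections side by side.**

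| Section | What it fixes for SCT, intervention vs control |
|---|---|
| Sample size calculation | Outcome is change; sized without covariates |
| Statistical methods | t-test; regression listed for associations only |
| Measurement tools | Age required as a covariate |

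The first two rows agree with each other. The third does not fit them.

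**3. Possible gain from adjusting for baseline SCT.** The correlation r between baseline and follow-up SCT is not given, so it is assumed. With equal variances s² at both times, the variance of change is 2s²(1 − r) and the ANCOVA residual variance is s²(1 − r²). Their ratio is (1 + r)/2, so the effective SD is 3 × √((1 + r)/2). Exact-t power, 22 per arm, two-sided 2.5%, before clustering:

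| r | Ratio | Effective SD | Power |
|---|---|---|---|
| t-test on change | 1 | 3.00 | 77.7% |
| 0.9 | 0.95 | 2.92 | 79.9% |
| 0.7 | 0.85 | 2.77 | 84.5% |
| 0.5 | 0.75 | 2.60 | 89.0% |
| 0.3 | 0.65 | 2.42 | 93.1% |

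The r = 0.9 row is a bound: with SD of change 3 it implies s = 3/√0.2 = 6.7 ml/s, and values between 0 and 10 cannot have an SD above 5.

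**4. Without equal variances.** Entry caps baseline SCT below 10 ml/s and follow-up has no such cap. With illustrative SDs of 2.5 and 4 and r = 0.6, the variance of change is 6.25 + 16 − 12 = 10.25 and the ANCOVA residual variance is 16 × (1 − 0.36) = 10.24. The ratio is 0.999, so there is practically no gain.

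**5. Age alone.** If age explains 5%, 10% or 20% of the variance of change (assumed), power at 22 per arm is 79.9%, 82.2% or 86.8%.

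**6. Effect of chance baseline imbalance.** Under equal variances s = 3/√(2(1 − r)), and the standard error of the baseline difference is s × √(2/22). An imbalance of one standard error shifts the change-score estimate by (1 − r) times that amount:
- r = 0.3: 0.7 × 2.54 × 0.302 = 0.54 ml/s (19% of 2.8)
- r = 0.5: 0.5 × 3.00 × 0.302 = 0.45 ml/s (16%)
- r = 0.7: 0.3 × 3.87 × 0.302 = 0.35 ml/s (13%)

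In the case of step 4 the slope is 0.6 × 4/2.5 = 0.96, and the shift is 0.04 × 2.5 × 0.302 = 0.03 ml/s.

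**The case against.** The strongest reply is that no sentence says outright that the primary SCT analysis is a t-test on change. The wording in Statistical methods is generic, the regression listed there could carry arm, age and baseline SCT, and a condensed article commonly leaves the covariates of the primary model to a fuller document. This stands in part: a reader might infer that the plan rules out age adjustment, and it does not. What remains is not an omission. The article names a test for intervention versus control and separately states a requirement which that test cannot meet.

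A reader might also infer that the baseline SCT goes unused. It does not: the change score subtracts it for every participant. The fair criticism is that its coefficient is fixed and possibly inefficient.

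Nor do the documents support saying that the t-test is biased. Under randomization the change-score contrast is unbiased overall; the shifts in step 6 are conditional on the imbalance that happens to occur, and vanish when the slope is near 1.

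Finally, it is tempting to claim that a model over both follow-ups solves the expected losses from death. It retains the 5-week data of people lost later, but does nothing for those lost before 5 weeks, and its 6-month contrast assumes missing at random, which is debatable for deaths.

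**Conclusion.** The conflict between Statistical methods and Measurement tools is real, concerns the primary outcome of part 2 and rests on no outside figure. Adding baseline SCT as well as age is advisable.

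Its benefit is uncertain. Power at 22 per arm before clustering rises from 78% to about 80–93% for r from 0.9 to 0.3, if baseline and follow-up variances are equal. It stays at about 78% if follow-up is markedly more variable, which the entry cap makes plausible. The documents give neither the correlation nor the two variances, so no single gain can be claimed. The stated 22 per arm is correctly computed for the unadjusted comparison.

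**What to change.** Reconcile the two sections by naming one primary analysis for part 2: a linear regression (ANCOVA) of SCT at each follow-up on arm, baseline SCT and age, with participants analysed by the allocation of their unit and with allowance for care unit. Keep the unadjusted t-test on change as a sensitivity analysis.

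The allowance for unit needs care. If the 32 units split equally (an assumption), 22 participants over 16 units is about 1.4 per unit, and a unit variance may be barely estimable. The plan should say what is done in that case.

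A repeated-measures model over both follow-ups is an option for keeping the 5-week data of people lost before 6 months, with its missing-at-random assumption stated.

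The cost is wording and a standard model. Both covariates are already collected, and they use two of the 42 residual degrees of freedom (44 participants less two arm means). Any precision gained should be kept as a margin and not used to lower the sample size.

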## Abbreviations

HRQoL: Health-related quality of life
Katz-ADL: Katz activity of daily living
MEONF-II: Minimal eating observation and nutrition form –version II
OHIP-14: Oral health impact profile
QoL: Quality of life
QPP: Quality of care from a patient perspective
RDH: Registered dental hygienist
ROAG: Revised oral assessment guide
SCT: Swallowing capacity test
SLP: Speech-language pathologist
SWAL-QoL: Swallowing quality of life questionnaire
